## Abstract

**Background:**

Families with low incomes experience an array of health and social challenges that compromise their resilience and lead to negative family outcomes. Along with financial constraints, there are barriers associated with mental and physical health, poorer education and language. In addition, vulnerable populations experience many services as markedly unhelpful. This combination of family and service barriers results in reduced opportunities for effective, primary-level services and an increased use of more expensive secondary-level services (e.g., emergency room visits, child apprehensions, police involvement). A systematic review of effective interventions demonstrated that promotion of physical and mental health using existing service was critically important.

**Methods/Design:**

The Families First Edmonton Trial (FFE) tests four service integration approaches to increase use of available health and social services for families with low-income. It is a randomized, two-factor, single-blind, longitudinal effectiveness trial where low-income families (1168) were randomly assigned to receive either (1) Family Healthy Lifestyle plus Family Recreation service integration (Comprehensive), (2) Family Healthy Lifestyle service integration, (3) Family Recreation service integration, or (4) existing services. To be eligible families needed to be receiving one of five government income assistance programs. The trial was conducted in the City of Edmonton between January 2006 and August 2011. The families were followed for a total of three years of which interventional services were received for between 18 and 24 months. The primary outcome is the number of family linkages to health and social services as measured by a customized survey tool “Family Services Inventory”. Secondary outcomes include type and satisfaction with services, cost of services, family member health, and family functioning. Where possible, the measures for secondary outcomes were selected because of their standardization, the presence of published norming data, and their utility as comparators to other studies of low-income families. As an effectiveness trial, community and government partners participated in all committees through a mutually agreed upon governance model and helped manage and problem solve with researchers.

**Discussion:**

Modifications were made to the FFE trial based on the pragmatics of community-based trials.

**Trial registration number:**

ClinicalTrials.gov NCT00705328

## Background

A pervasive challenge faced by Canadian health and social service providers is to promote health for vulnerable populations in a proactive and cost-effective manner. Indeed, families with low incomes continue to experience an array of health and social barriers that compromise their resilience, leading to negative family outcomes, and inhibiting access to available services. The relation between low income and poor health is well known. In a recent systemic review, researchers found higher rates of mental health problems among children with low socioeconomic status [1]. The Canadian infant mortality rate is two-thirds higher in low-income neighbourhoods than in the highest income neighbourhoods [2]. Low-income Canadian children are more likely than their higher-income peers to suffer from ill health and mental illness [3], to be hospitalized [4], to have lower levels of cognitive scores and educational attainment [5], to have compromised memory and self-regulation [6], and to experience major behavioural problems [6-15]. Living with a low income compromises parental health and ability to parent, threatens family resilience, and jeopardizes family-community relations [16,17]. The health of low-income parents influences their ability to attain and maintain employment [18-23]. In addition, the constraint in public expenditure and commensurate movement away from universal services [24], which began in the 1990s, continues to affect those living with low incomes the most.

### Low-income and the social determinants of health

Based on decades of inquiry, the World Health Organization [25], the Public Health Agency of Canada [26], and the Canadian Medical Association [27] have agreed that health and well-being are largely shaped by social and economic contextual factors, which are collectively referred to as the “social determinants of health.” Contextual factors such as low educational attainment and low-wage precarious employment negatively influence the health of low-income families and their members by limiting their capacity to (a) increase their income and (b) obtain and use health and social services.

### Increasing income

Despite growth in the Canadian economy during the mid 2000s, which resulted in an increase in jobs and a decline in unemployment rates [28], the incidence of low income among Canadian families remains essentially unchanged [29,30]. Further, in Canada, having work does not preclude having a low income. For instance, in two-parent families with one earner, 23% have low incomes [31]. In female-headed single-parent families where the mother is employed, 43% are living on low incomes [32]. In Edmonton, the site of the study, 18.5% of families and 26.5% of children have low income [33]. Provincially, decision-makers are interested in providing services to low-income families that are both beneficial and cost effective [34] (e.g. Alberta’s Social policy framework [35] and the Results-based Budgeting initiative [36]).

Moving social assistance recipients from welfare to employment was a main goal of the 1990s social policy reform across Canada. In these programs low-income recipients of social assistance are required to get jobs or engage in employability programs [37-40]. Evaluative studies of welfare-to-work initiatives in Canada and the U.S. [21,22,41-44] suggest that policy efforts to move parents from social assistance to employment have been successful [22,42,44,45] but do little to ameliorate the negative health consequences of living on a low income. That is, welfare-to-work programs seem to influence parents’ health and children’s development only when increased parental employment is accompanied by increases to family income [17,22,41,44]. There are two ways to increase income in working families: increase income from employment and provide income supplements, such as the Self-Sufficiency Project [42,44]. The majority of parents who move from social assistance to employment plus income supplement continue to have family incomes below low-income cut-offs. Furthermore, their income tends to decline when supplements end [42,44,46]. Finally, the evidence is mixed on the effects of welfare-to-work programs on children [17,22,41,44,47].

Evaluation studies of welfare-to-work continue [48] but controversy remains [49-51] because of the many unintended consequences of these programs. Insights from recent studies reveal that single low-income parents face significant day-to-day challenges when integrating work and family demands, such as arranging child care [52]. Further, the transition from welfare to work emphasises economic issues (lack of health benefits) that are a root cause of welfare dependency [53].

### Obtaining health and social services

Since welfare-to-work initiatives, with or without income supplements, do not impact health in low-income families in a sustainable way, there is a need for interventions that are directly guided by the goal of enhancing health. The benefits of participating in health and social programs are well documented [46,54-58]. A consistent relation exists between family socioeconomic status and engagement/retention rate of families in health, social, educational, leisure, and cultural activities [7,8,59-61].

Barriers to the use of community-based health and recreation services cause low-income families to use primary health prevention and promotion services, including community resources and recreation, less often than other income groups [46,62-65]. For these families, personal barriers include (a) financial constraints, (b) under or unemployment, (c) mental and physical health problems, and (d) challenges to quality of life, such as communication difficulties associated with poor education and language barriers [66-70]. Families that overcome personal barriers often face barriers at the system level that include: fragmentation; narrowness of mandate; power differential created by provider expertise; and difficulty in access because of location, language, and hours of availability. Such service barriers lead to suboptimal outcomes and use of more expensive downstream societal resources.

In summary, low-income families face barriers to increasing their income and to obtaining a broad range of health and social services, thus negatively influencing their health and social outcomes. The evidence reviewed indicates that increasing access to service may be a direct and sustainable way to improve health and social outcomes in low-income families. An important goal for Canadian society must be to develop service-delivery policies and practices that reduce barriers to linkages between services and families in need, while being cost effective. This study focused on service integration approaches that actively link low-income families to healthy family lifestyle (e.g., health services, child care/schools, social supports) and to recreation.

### Families first Edmonton trial

In the Families First Edmonton (FFE) trial, we randomized 1168 low-income families into four service integration approaches to test proactive linkages between low-income families and services existing in their communities.

### Family healthy lifestyle and family recreation as service integration approaches

FFE was initiated after findings from When the Bough Breaks (WTBB), an award-winning Canadian study [24], were published. That study showed that that providing low-income families on social assistance with proactive comprehensive care (health promotion, employment retraining, and recreation activities for children) compared to allowing families be self-directed in finding these services, resulted in 15% more exits from social assistance within 1 year and substantial savings to society in terms of social assistance pay-outs.

Primary health care is the first element of continuing health and is designed to connect families to community services concerned with the broad determinants of health, including health services, education, and social support [71,72]. It is accessible, continuous, comprehensive, and coordinated, and is provided as closely as possible to where people live or work. Primary health care delivered through in-house family support has been shown to enhance both parents’ [13,73,74] and children’s well-being [73,75-78]. Social support accounts for a significant proportion of low-income family adaptation [79,80]. It is likely that parental involvement with childcare and schools leads to a richer family social support network [81-83]. More importantly, it has also been found that children whose families are linked to their schools have better academic achievement [83].

Regarding recreation, children who are active and engage in positive recreational opportunities benefit in physical well-being, psychosocial health (e.g., less anti-social behaviour), and resilience [13,14,84-89]. The lack of skill development programs for low-income children imposes short- and long-term negative consequences [69]. Children’s participation in recreation is also linked to positive impacts on family relationships [69,90] and parental adjustments that are related to positive child development outcomes [74,84,91].

The FFE investigation tested the findings and probed the conditions and generalizability of WTBB for current social assistance environments. FFE differs from WTBB in many ways. First, an analytic framework that describes the outcomes and intervening variables founded the research questions and plan for data analysis. Second, the primary health care and recreational service integration approaches and supporting practices were described in detail and closely audited to enable transfer of the successful service integration approach. Third, the sample aimed to be more inclusive to allow for examination of a broad socio-economic profile of low-income families, thus allowing researchers to address the question of who benefits the most and under what circumstances, questions typically neglected in this type of research [92]. WTBB included only single-parent families (98.1% female-headed) on social assistance. FFE included both single- and two-parent families. WTBB was conducted prior to the implementation of mandatory welfare-to-work initiatives. In Alberta, welfare-to-work initiatives require low-income families who receive income support to engage in employment or employment-related activities in exchange for income support once their youngest child is 12 months of age. Further, the sample from WTBB was predominately Euro-Canadian. FFE recruited participant families in an area where 54% of Edmonton’s Aboriginal population and 39% of Edmonton’s visible minorities reside, thus allowing for analysis based on these characteristics. Families who do not speak English were given the opportunity to participate. Fourth, the role of family functioning was explored as an intervening variable between the service delivery models and the primary outcome (family linkage to services) and to secondary outcomes (costs and health). Fifth, the service delivery models in WTBB were implemented for one year. In FFE, the models will be implemented for up to two years with follow-up for three years. This design facilitated examination of short-, intermediate-, and longer-term outcomes. Sixth, the service delivery models of FFE were designed by service delivery professional and researchers to be simple, transparent, easily tracked, and sustainable. Thus FFE was designed to generate the types of knowledge that will be essential if FFE interventions are to be adapted and implemented elsewhere.

### Principles of service integration practice

A systematic review of effective interventions for school-aged children, 29 reviews of 1102 intervention studies [93], drove the selection of practice principles for service integration practices within the content areas of Family Healthy Lifestyle and Family Recreation. The studied interventions encompassed a variety of program orientations including promoting physical and mental health, enhancing educational outcomes, fostering positive emotional adjustments, and preventing problem behaviours, suicide, and child abuse. Analysis showed that successful programs have seven characteristics. First, they were holistic and integrated. The complexity of the life of the child, parent, and family is addressed. Intervention strategies that target diverse areas (e.g., mental and physical health, safety, education, recreation, and youth employment) are needed. Second, successful programs resulted from collaborations that are multi-level and multi-sectoral. Third, successful programs were capacity building. They provide opportunities to build skill, rather than focusing exclusively on eliminating undesirable problems and behaviours. Fourth, successful programs were client-centred. For example, culturally appropriate services are offered and transportation barriers are addressed. Fifth, successful programs were community-based in what is available and situated in families’ neighbourhoods. Sixth, successful programs were long term, engaging at-risk children and youth long enough to show effects and enabling relationships between staff and participants to develop. Seventh, successful programs were well staffed with supportive personnel who are culturally similar to the population served. As a result, the practice principles selected to be embedded in the service integration content areas of Family Healthy Lifestyle and Family Recreation included family-centredness, cultural sensitivity, capacity building and reflection.

### Aim of the study

This study focused on evaluating service integration approaches directed at increasing linkages between low-income families and services existing in their communities. The primary research question was:

What are the effects of three community-based service-integration approaches (Family Healthy Lifestyle, Family Recreation and Comprehensive), as compared to a control model (Existing Services), on the number of linkages that families initiate and maintain with established health and social services?

The design of the study enabled a thorough examination of several additional questions that are critical for understanding the influence of different service-delivery models on family linkages with established services, costs, and health. Secondary research questions included:

1. What are the relative effects of different service integration approaches on specific characteristics of family linkages to established service (e.g., type of service, satisfaction with), and how do the frequency and type of involvement change over time?

2. What are the costs to service systems of each of the service-integration approach over time?

3. What are the physical and psychosocial health outcomes of family members, over time, associated with each of these service integration approaches?

In order to effectively contribute to policy change, it was important to identify concurrent and antecedent variables related to linkage, cost, and health outcomes, and to estimate the likely impact of these variables [94,95]. Tertiary research questions included:

4. What is the intervening role of family functioning (family problem solving, communication, parenting, connections to community) between each of the four service integration approaches and linkage to services, cost, and health outcomes for family members, and how does this role change over time?

5. To what extent does sociodemographic profile (e.g., ethnicity, immigrant status, education, occupation, family type, level of income, sources of income, security of housing, number of children) influence the relation between each of the four service integration approaches and linkage to service, cost, and health outcomes, and how does this influence change over time?

### Hypothesis

We hypothesized that low-income families who receive community-based service-integration (i.e., Family Healthy Lifestyle, Family Recreation and/or Comprehensive) would initially increase linkages to services, and that costs to service systems would decrease as improvements to physical and psychosocial health of family members are realized over time.

## Methods/Design

### Study design

FFE is a randomized, single-blind, longitudinal effectiveness trial with a 2 by 2 factorial design with three integration groups and a control group. The study was conducted in the City of Edmonton between January 2006 and August 2011. The study employed a multi-prong strategy to recruitment. Eligible families were invited to the study through five source programs for low-income families. In addition, posters and invitation packages were available at community agencies and through service workers. Information about the study was presented at community events where eligible families could inquire for more information. All families who received the source programs during the recruitment period were invited to participate in the study. Families were randomized after baseline data collection using a 1:1:1:1 allocation ratio. Those who were assigned to the intervention groups received between 18 and 24 months of service integration intervention. All families were followed by researchers for a total of three years with a minimum of ten interviews for data collection: two at baseline, and two at year 1, year 2, and year 3, respectively.

### Eligibility criteria for participants

The study focused on low-income families residing in City of Edmonton. To be eligible families needed to be receiving one of the five government assistance programs: (1) Income Support (“social assistance”), (2) Alberta Child Health Benefit, (3) City of Edmonton’s Leisure Access program, (4) Alberta Adult Health Benefit, and (5) Capital Regional Housing. All these programs provide either financial assistance or access to affordable housing and recreation for low-income individuals or families in the city area. In addition, potentially eligible families would have at least one child younger than 12 years of age living in the household. Families were allowed to define themselves: thus, the definition of family is not confined to traditional dual-parent family or biological-parent family but includes others such as single-parent families, adoptive families, and grandparent led families.

### Exclusion criteria

At recruitment, the study had three main exclusion criteria: (1) unwilling to commit to the full length of the study, (2) unwilling to provide researchers access to the focus child, or (3) non-English speaking families for whom researchers were unable to locate a relevant interpreter. After families were recruited, they were free to withdraw from the study at any time without penalty, with the understanding being that the intervention to which they were assigned was terminated. Although the study focused on low-income status, families with sufficient improvement in household income were not excluded from the study, due to recognition of income fluctuation in some vulnerable populations. After recruitment, families were no longer eligible to participate if they moved outside of the study area, the City of Edmonton.

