### Statistical methods

Most analyses will follow the intent-to-treat principle. The last-observation-carried-forward method will be used to impute missing data to maintain the integrity of the data set. Data will be analyzed using Stata MP 13.0 and SPSS 21.

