**Figure 1 F1:**
[figure not shown]
Participant flow.

Of the families who were contacted and expressed interests in the study, 1282 families were successfully screened and met recruitment criteria. Because some families withdrew and contact with others was lost, only 1168 families were randomized into the four groups.

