### Losses and exclusions after randomization

As indicated in Figure 1, during the process participants could either withdraw (i.e., lost to follow-up) or be ‘dormant’ for some of the data collection points (i.e. unavailable). At 36 months we were able to collect data from 748 families; data from 414 families were lost (135 Existing Services, 88 Family Recreation, 110 Family Healthy Lifestyle, and 91 Comprehensive). Table 2 shows reported reasons for withdrawal.

**Table 2 T2:** Losses and exclusions

**Reasons for withdrawal**	**Before randomized**	**After randomized**	**Reasons for withdraw (count)**
Not interest in	55	18	73
Too busy/No time	47	40	87
Move out of study area	10	88	98
Family circumstances	8	9	17
Problems with research	6	4	10
Problems with randomized design	5	-	23
Problems with services allotted	-	18	18
Health	3	5	8
Kids not interests in	3	1	4
Too much time past since last contact	3	0	3
Cultural differences	1	0	1
Stigmatization	0	1	1
Unknown	18	5	23
**Grand Total**	**159**	**189**	**366**

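### Families who left Edmonton after randomisation stopped being observed, and the plan fills their later outcomes by carrying the last value forward

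*Protocol article*

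**What the plan says.** All references are to the protocol article.

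- Exclusion criteria: "After recruitment, families were no longer eligible to participate if they moved outside of the study area, the City of Edmonton". The same section keeps families whose income improves, so one kind of change after entry is tolerated and another ends participation.
- Study design: "Families were randomized after baseline data collection using a 1:1:1:1 allocation ratio". The period after recruitment therefore runs from before allocation to the end of follow-up. The same section says: "All families were followed by researchers for a total of three years".
- Statistical methods: "Most analyses will follow the intent-to-treat principle", and "The last-observation-carried-forward method will be used to impute missing data to maintain the integrity of the data set".
- Losses and exclusions after randomization, Table 2: the row "Move out of study area" shows 10 families before randomisation and 88 after.
- Participant flow: "only 1168 families were randomized into the four groups". Month-36 data were collected from 748 families.
- Hypothesis: linkages are expected to rise at first, with cost and health effects following over time.
- Blinding: families knew their allocation, and investigators were unblinded in January 2012.

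**The concern.** An eligibility rule was applied to families already randomised, and it was triggered by an event that happens after allocation. Moving is unlikely to be unrelated to the outcome. The article itself lists housing security and income among the characteristics that may alter the relation between approach and linkage, and one source programme is a housing programme. Families also knew their arm.

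Once a family leaves, its later linkage counts are missing, and the stated repair is to carry the last one forward. The carried value is a poor guess for an outcome that the trial expects to change between annual measurements. It also enters the model as if it had been observed, so standard errors come out too small. At stake are the year-2 and year-3 contrasts between the service-integration arms and existing services.

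**Working it through.** **1. Table 2, column after randomisation.** 18 + 40 + 88 + 9 + 4 + 0 + 18 + 5 + 1 + 0 + 0 + 1 + 5 = 189, which agrees with the printed total. The next largest reason after moving is lack of time, with 40. (The printed overall total of 366 differs from 159 + 189 = 348 because of a different row. Neither 88 nor 189 is affected.)

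**2. Share due to moving.**

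- Of recorded withdrawals after randomisation: 88/189 = 46.6%.
- Of families randomised: 88/1168 = 7.5%.
- Of families without month-36 data: the article gives 414, its arm counts sum to 135 + 88 + 110 + 91 = 424, and 1168 − 748 = 420. The share is 88/424 = 20.8%, 88/420 = 21.0% or 88/414 = 21.3%. These are upper limits, because they assume that every mover lacks month-36 data.
- Families without month-36 data and without a recorded withdrawal reason: between 414 − 189 = 225 and 424 − 189 = 235.

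(The 88 movers and the 88 month-36 losses in the Family Recreation arm are different counts.)

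**3. What carrying forward does.** Data were collected at baseline and at years 1, 2 and 3.

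| Family moves | Year 1 | Year 2 | Year 3 |
|---|---|---|---|
| before year 1 | baseline | baseline | baseline |
| between years 1 and 2 | observed | year 1 | year 1 |
| between years 2 and 3 | observed | observed | year 2 |

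Services ran for 18 to 24 months. In the second row a count taken while services were running therefore stands in for a year when they had ended. In the first row any early rise is erased. The two cases can push in opposite directions.

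**4. Bias at year 3.** For an intervention arm T and control C, let p be the proportion of movers and d the mean carried value minus the mean true value among movers, in SD units. The bias in the contrast is p_T × d_T − p_C × d_C. The article gives none of these four quantities; only the overall p, 7.5%, is known. Two illustrations follow, in which every other input is assumed:

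- Movers 10% v 5% and the same d of 0.3 to 0.5 SD in both arms: 0.05 × 0.3 = 0.015 to 0.05 × 0.5 = 0.025 SD.
- Movers 7.5% in both arms, d of 0.3 to 0.5 SD in one arm and 0 in the other: 0.075 × 0.3 = 0.023 to 0.075 × 0.5 = 0.038 SD.

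The second case shows that bias does not need unequal moving. For scale, f = 0.10 across four equal groups implies a largest contrast of at least 2 × 0.10 = 0.20 SD.

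**5. Loss by arm.** With 1168/4 = 292 families per arm, month-36 loss is 135/292 = 46% in Existing Services, 88/292 = 30% in Family Recreation, 110/292 = 38% in Family Healthy Lifestyle and 91/292 = 31% in Comprehensive. Loss is uneven. How much of the unevenness comes from moving cannot be seen.

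**6. The plan's power figure.** N = 4 × 300 × 0.75 = 900 and f = 0.10 give noncentrality 900 × 0.01 = 9. The F test with 3 and 896 degrees of freedom at 0.05 then has power 0.709, against 0.72 stated. The figure reproduces and does not depend on the moving rule.

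**The case against.** A reader might infer that movers are dropped from the analysis, so that the rule breaks intention to treat outright. The article does not support that. It ends participation, tabulates movers among reasons for withdrawal, and promises imputation for missing data, which points to keeping them. The word for most analyses does not place the primary analysis outside the principle, and a fuller definition of the analysis set may be in a document not shown.

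A reader might also infer that carrying forward credits families with linkages known to have ended. The inventory takes a societal perspective and is nowhere restricted to services in the city, so that does not follow either.

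Nor should the lost follow-up be costed as recoverable. Had all 88 movers been observed at month 36, data would number 748 + 88 = 836, and power at f = 0.10 would be about 0.67 rather than 0.62. That is an upper bound on a complete-case calculation. Data collection ended in 2011, and the primary instrument was given face to face over two home visits. A geographic limit was a reasonable choice for such a trial.

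Finally, about 79% of families without month-36 data are not recorded movers, so the weakness of carrying forward is general, and the illustrated bias is small. Both points stand. They limit the size of the concern but do not remove it: for movers, the trial's own rule created the gap and the article itself fixes how to fill it.

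**Conclusion.** The rule ended observation of 88 randomised families, the largest recorded reason for withdrawal after randomisation but not most of the loss. It contradicts the statement that all families were followed for three years, and the two sections must be reconciled. The stated imputation then freezes a baseline or early count through year 3 for families whose moving is plausibly linked to housing, income and arm.

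The size and direction of the resulting bias cannot be computed. Under the assumed inputs above it is 0.015 to 0.038 SD, at most about a fifth of a 0.20 SD contrast (0.038/0.20 = 19%). This is a modest weakness with a cheap remedy, not a failure of the randomised comparison. The link between moving and outcome is a judgement drawn from the article's own list of influencing variables and is not shown by data.

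**What to change.** - State that the primary analysis includes all 1168 families in the arm to which they were randomised, with every observation collected before a move.
- Replace carrying forward for post-move windows. Treat them as missing in a likelihood-based repeated-measures model (a mixed model for counts if the Poisson route is taken), or use multiple imputation with baseline housing security, income source and prior linkages as predictors. The same model can serve other missing windows.
- Report movers by arm and, where the data allow, by year of move.
- Add one sensitivity analysis under a missing-not-at-random assumption: shift movers' post-move linkages over a stated range, separately by arm.
- Correct the Study design sentence to say that follow-up was planned for three years and ended early for families who left the city.
- Date the change and label it as made after the January 2012 unblinding.

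The work uses data already held. It costs a few sentences, one extra analysis and somewhat wider intervals than single imputation gives. The main model would still assume that, given the variables used, post-move values are missing at random; the sensitivity analysis is there to test that.
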